#### Intervention feasibility measures.

*Recruitment rates*

Refers to the number of participants able to join the therapy as a result of the recruitment process.

*Participation rates*

Participants who completely discontinue therapy should be classified as dropouts.

*Questionnaire feasibility*

The feasibility of the questionnaires will be measured by evaluating the completion rates of the questionnaires including client feedback and the degree of missing data.

*Homework evaluation*

To assess the value of homework, an adapted version of the Homework Rating Scale (HRS) [55] will be employed, consisting of seven questions rated on a 5-point Likert scale. Participants will be asked to evaluate their level of achievement, understanding, effort, utility, relevance, satisfaction, and the impact of the exploratory tasks assigned during the therapy weeks [22].

#### Exploratory outcomes.

The exploratory results encompass the primary outcome variables of forgiveness and letting go, as well as the secondary outcome variables of quality of life and depression.

*Enright Forgiveness Inventory*

The Enright Forgiveness Inventory (EFI) [10] is a self-report measure designed to assess the level of forgiveness in response to a specific offending situation. The scale begins by asking participants to visualize the personal offense and imagine what happened. In a second phase, participants are asked to describe the offense in their own words. The EFI scale comprises 60 items organized into three 20-item subscales that measure affect, behavior, and cognition related to forgiveness, and a final 6-point Likert scale known as the Attitude Scale. Finally, the EFI concludes with a final question assessed on a 5-point Likert scale, which evaluates the extent to which clients report having forgiven their injurer.

*Letting Go Measure*

The Letting Go Measure [3] is a self-report assessment comprising a single item. It evaluates the extent to which individuals have let go of their negative emotions towards the injurer. Scores range on a Likert scale from 1 to 5 points.

*Quality of Life*

The European Portuguese World Health Organization Quality of Life Assessment in Older Adults (WHOQOL—OLD) [55,56] comprises 28 items classified on a five-point scale and encompassing seven domains: sensory, autonomy, activities, social, death, intimacy, and family life [56].

*Geriatric Depression Scale*–*15*

The Geriatric Depression Scale–15 (GDS-15) [57,58] is specifically designed for screening depressive symptoms in older adults. It consists of 15 straightforward questions, each requiring a simple Yes or No response. The scale ranges from zero (indicating no depressive symptoms) to 15 points (representing the highest severity of depressive symptoms), with each affirmative response scored as 1 point. The cut-off points are defined as follows: 0–4 for the absence of depressive symptoms, 5–8 for mild symptoms, 9–11 for moderate symptoms, and 12–15 for severe symptoms [58].

### Data handling and storage

The data protection plan, approved by the Ethics Committee of the University of Maia—with the ethical board granting approval under the number 40/2022—ensures that participants are informed about the study’s objectives, confidentiality, and data management procedures, and sign an informed consent form. Consent forms will be securely stored in the corresponding author’s office. Participants will be assigned codes, and their names kept separate from other data. The collected data will be stored in a locked box within a securely closed cabinet, to which only the author has access. This cabinet is located in the investigator’s personal workspace, with no access permitted to third parties. Data will be digitized for analysis, with stringent accuracy checks and password-protected access for trial staff. Audio and video recordings will be securely stored and destroyed six months post-therapy. Any changes to data handling will be reviewed by the ethics committee [22,29].

### Data collection

As illustrated (Fig 2), various measures will be administered throughout the study—from participant selection to the two planned follow-up assessments. To minimize the burden on participants, questionnaires scheduled for completion at the end of the therapy will be distributed either during the final session or at home between sessions. The questionnaires will be returned in sealed envelopes to the therapists, who will then hand them over to the psychologist responsible for the evaluation process. This independent psychologist will also conduct the initial assessment for study integration and the final qualitative interview [22,29].

To efficiently assess whether potential participants meet the study criteria, eligible individuals will undergo the Structured Clinical Interview for DSM-5—Research Version (SCID-5-RV) [59] and the Montreal Cognitive Assessment (MoCA) [37,38]. Additionally, socio-demographic data, including age, gender, occupation, religious beliefs, current medications, and details regarding the interpersonal offense or emotional injury experienced, will be collected at the outset [22,25,34].

After participants are assigned to their respective groups, three assessment points will be established: before therapy begins, at the sixth session, and at the final session. These assessments will focus on Forgiveness, Letting Go, Quality of Life, and Depression. Before therapy commences, the CEQ will also be administered. Following each session, the Satisfaction Therapy Module and Homework Evaluation will be conducted. Upon completion of therapy (t3 and t5), the CCIP will be administered. To ensure adherence to the therapy protocol, sessions will be recorded for subsequent supervisory evaluation [22,29,34]. Research assistants will provide updates and reminders for follow-ups via telephone and/or email.

### Statistics and data analysis

#### Quantitative analysis.

Quantitative data analysis will be conducted using SPSS version 29.0 for Windows [60]. Given the study’s exploratory character, particularly with regard to its secondary objective—namely, the study of treatment outcomes—the primary focus is not to test formal hypotheses but rather to provide an initial descriptive overview of the data [22,25]. Accordingly, we have chosen to employ descriptive statistics such as means, standard deviations, frequencies, and percentages to summarize the results. By prioritizing descriptive statistics, we seek to maintain methodological rigor while offering meaningful insights that may inform future, more comprehensive and definitive investigations [35,34].

The ratio of individuals who accepted the invitation to participate in the study relative to the total number of formal invitations sent will help determine the recruitment size. It is anticipated that accurately quantifying the total number of individuals reached through various channels may prove challenging. Additionally, the ratio of participants who complete therapy compared to those who initially commenced it will offer insights into retention rates. Furthermore, the completion rates of the questionnaires will serve as an indicator of their feasibility. Other measures, including assessments of acceptability and feasibility—such as the CEQ, CCIP, Session Satisfaction Module, and Homework Evaluation—will be assessed through exploratory data analysis [22,25,29,34].

To identify and quantify potential associations among the different variables for the main trial, Pearson correlations will be performed to analyze observed changes over time in the control group for all outcome variables. The calculation of the sample size for a future large-scale randomized controlled trial will be guided by the statistical power required to detect clinically meaningful effects, rather than by the provisional estimates derived from this feasibility study [35].

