## Abstract

Over recent decades, Emotion-Focused Therapy, aging, and forgiveness have garnered significant attention in the field of psychology. However, there is a lack of studies on Emotion-Focused Therapy and forgiveness specifically tailored for older adults. This article presents a protocol designed to assess the feasibility and acceptability of a randomized controlled trial of Emotion-Focused Therapy aimed at resolving emotional injuries in individuals aged 65 and older, within the context of interpersonal offenses. Feasibility will be evaluated through recruitment and retention rates, as well as adherence to the intervention protocol. Acceptability will be assessed based on perceived treatment credibility, participants’ expectations regarding outcomes, levels of engagement, and overall satisfaction with the intervention. The study is structured as a two-arm, parallel-group randomized trial with a waiting list control. We propose recruiting a sample of 70 participants, randomly assigned to either an immediate intervention group, which will receive Emotion-Focused Therapy over twelve weekly sessions, or a control group that will receive the same therapy after a twelve-week waiting period. Data will be collected in the beginning, middle, and at the end of therapy, and in two planned follow-ups (three and six months after therapy). Once this protocol is implemented, if the therapy proves to be feasible, acceptable, and shows promising results, the findings will inform a large-scale randomized clinical trial to advance the understanding of this treatment for individuals aged 65 + .

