### Participants

Our feasibility study will include a minimum total sample of 70 older participants, with 35 randomly allocated to the intervention group (IG) and 35 to the waitlist control group (CG) [22,29]. Although feasibility studies do not require large samples [33], they should adequately represent the target population and be sufficiently large to fulfill the study’s objectives. Authors [33,30,31] agree that feasibility RCTs typically recruit between 24–50 participants per arm on average, with the exact number depending on the specific aims and objectives of the study. Larger sample sizes may be necessary for more complex or ambitious goals (in accordance with the G*Power requirements for comparing two groups) [33,30,31].

Given the exploratory nature of our study—aimed at evaluating the feasibility and acceptability of the therapy, as well as obtaining preliminary insights into its potential effectiveness among the participants involved, rather than establishing causality or generating generalizable results—we determined that a sample size of 70 participants would be appropriate. This decision was informed by precedents in comparable feasibility studies [22,29,34], as well as by practical considerations such as recruitment capacity, budgetary constraints, and the minimum sample size required to adequately address feasibility-related objectives [35]. Based on all of this, we propose to include 80 individuals in our study to ensure that at least 35 participants complete each comparison group (minimum N = 70). Therefore, in line with other studies, an additional 15 percent of participants will be recruited to account for typical dropout rates [9,13].

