### Progression criteria

This study protocol will be developed for broader research based on the assessment of its acceptability and feasibility. Regarding the CEQ measure, the study will proceed without changes if the result is ≥ 6 on a 9-point Likert scale. The study will also progress without changes in the Session Satisfaction Module if the result is ≥ 3 on a 5-point Likert scale [22]. For recruitment, the progression criterion will be a rate of 75–100% of the sample size [61]. The criterion for retention level will be a rate >80% [36]. The progression criterion for the questionnaires will be a response rate >90%. For homework assessment, a score of ≥ 3 on a 5-point Likert scale will be required [22,29].

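### The only retention definition counts therapy completers among those who started therapy, so the >80% criterion cannot register people lost between randomisation and therapy, notably controls during the 12-week wait

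*Protocol article*

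**What the plan says.** Retention rate is one of the primary feasibility indicators in the protocol article (Primary objectives). Three places bear on how it is measured:

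- Quantitative analysis: "the ratio of participants who complete therapy compared to those who initially commenced it will offer insights into retention rates".
- Progression criteria: "The criterion for retention level will be a rate >80"%, with no denominator restated.
- Intervention feasibility measures, under participation rates: "Participants who completely discontinue therapy should be classified as dropouts". This presupposes that therapy was started.

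The comparison arm is "a control group that will receive the same therapy after a twelve-week waiting period" (Abstract). Study design adds that these participants are assessed while they wait.

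The Participants section plans on a different base: "we propose to include 80 individuals in our study to ensure that at least 35 participants complete each comparison group", and "an additional 15 percent of participants will be recruited to account for typical dropout rates". That reasoning runs from inclusion to completion, not from the first session.

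**The concern.** Half of those randomised cannot start therapy for twelve weeks. A control who leaves in that time, or an immediate-arm participant who never attends, is not a commencer and has discontinued no therapy. Such a person enters neither the numerator nor the denominator, so the stated ratio does not fall however many are lost this way.

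The ratio is a sound measure of therapy completion among starters. The main trial also needs to know whether randomised people in both arms can be kept to the end of the controlled comparison. The Abstract names retention and adherence as separate things, but the definition given for retention is one of adherence. The criterion could then be met while the control arm loses people at a rate that would trouble the main trial.

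**Working it through.** **Inputs from the article.** 80 to be included; at least 35 completers per group, so 70; 15% added for dropout; equal allocation, so 40 per arm at 80; retention bar >80%.

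**Assumptions.** Loss during the wait is not given and is varied below. All immediate-arm participants are taken to start, and completion among starters is varied from 85% to 95%.

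**The plan's own figure.** 70 × 1.15 = 80.5, which reproduces the stated 80. From inclusion, 80 falling to 70 is a loss of 10/80 = 12.5%, or retention of 87.5%. The planned allowance is therefore about 12.5–15% from inclusion to completion.

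**The two ratios.** Let R be the number randomised, S the starters and C the completers. The stated ratio is C/S and the ratio over all randomised is C/R. Since S = R − (losses before therapy), C/S = C/R when there is no such loss (70/80 = 87.5% both ways), and C/S > C/R otherwise.

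**Example (assumed).** 10 of 40 controls leave in the wait, so S = 70. Let C = 60.
- Stated: 60/70 = 85.7%, above the bar.
- Over randomised: 60/80 = 75.0%, below it.

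**When the result changes on completers over randomised.** C/R is at or below 80% only if total loss is at least 20% (16 of 80). The smallest loss during the wait that does this, with R = 80:

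| Completion among starters | Controls lost in wait (of 40) | C/R |
|---|---|---|
| 85% | 5 (12.5%) | 0.85 × 75/80 = 79.7% |
| 87.5% | 7 (17.5%) | 0.875 × 73/80 = 79.8% |
| 90% | 9 (22.5%) | 0.90 × 71/80 = 79.9% |
| 95% | 13 (32.5%) | 0.95 × 67/80 = 79.6% |

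If total loss stays within 12.5–15%, C/R is 85–87.5% and passes, however the loss is divided.

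**The same example at the end of the 12-week controlled period.** Here a control is retained if assessed at the end of the wait, and therapy dropouts are assumed to give no data.
- Immediate arm: 40 × 60/70 = 34.3, or 85.7%.
- Controls: 30/40 = 75.0%.
- Overall: (34.3 + 30)/80 = 80.4%.

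The overall figure just clears the bar and the control arm does not, which is why the result is needed by arm. On this measure, with completion r in the immediate arm and L controls lost, overall retention is (40r + 40 − L)/80. It is at or below 80% once L reaches 40r − 24: 10 of 40 at r = 85%, 12 of 40 at r = 90%. The control arm alone fails at L = 8, since 32/40 = 80%.

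**The case against.** The link between the ratio and the criterion is inferred. Progression criteria states no denominator, and the analysis section says only that the ratio gives insight into retention, which is loose for a formal definition. A fuller plan may be more exact. This stands as a caution, but the article offers no competing definition.

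A reader might infer that people lost before therapy disappear from the trial's reporting. The article does not support that. Study setting has attendance and dropouts analysed by intention to treat and for completers, with reasons for dropout recorded, and Study design commits to CONSORT. A shortfall against 35 completers per group would also be visible. The recruitment measure, "Refers to the number of participants able to join the therapy as a result of the recruitment process", might pick up some of the loss, though Quantitative analysis computes recruitment as acceptances over invitations. Questionnaire completion, with its own >90% criterion, could also fall if it is taken over all randomised. None of these enters the >80% retention figure.

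A reader might also infer that failing the criterion stops the programme. The article lists progression criteria and does not say what follows from missing the retention one.

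Finally, completion among starters is a legitimate indicator for an objective that concerns feasibility of the therapy and its assessment. That is right, and it is a reason to keep the ratio under its own name.

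**Conclusion.** The point holds as a mismatch between a stated measure and its purpose. On the only definition given, the >80% criterion reflects therapy completion among starters and cannot respond to attrition during the wait. It also uses a different base from the article's own sample-size reasoning.

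The size depends on a figure the article does not give. With no loss before therapy, the choice between starters and randomised makes no difference to the completion ratio. In the assumed example the gap is 85.7% against 75.0%. The documents do not show that the trial is likely to pass wrongly: on completers over randomised, total loss must reach 20%, against a planned 12.5–15%. Spending the whole 15% after therapy starts and adding loss during the wait on top would overstate the risk, because that allowance runs from inclusion.

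A reader might go further and conclude that the >90% questionnaire criterion cannot be met at the planned dropout. That would require leavers to return no questionnaires at any time point. The article does not say so, and it schedules an assessment before therapy begins.

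**What to change.** In Quantitative analysis and Progression criteria:

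1. Define retention for the >80% criterion over all randomised participants, overall and by arm, as the proportion assessed at the end of the 12-week controlled period.
2. Keep completers over starters as a separate therapy-completion (adherence) rate.
3. Report losses during the wait on their own line.

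The cost is about two sentences, and recruitment has not begun. Study design says waiting participants are assessed, so no extra data collection appears to be needed. However, Data collection ties the assessment points to therapy sessions and the schedule figures are not shown, so the authors should confirm that controls have an assessment at the end of the wait.

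The reported retention figure may be less favourable. With equal arms and the assumptions above, the overall figure falls below the stated ratio when the proportion of controls lost in the wait exceeds the proportion of starters who drop out. Otherwise it is equal or higher, because control-arm dropout after week 12 moves to the therapy-completion rate.

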#### Secondary objective.

a. To explore the outcomes of EFT for the resolution of emotional injury among the study’s participants, according to forgiveness and letting go measures (primary outcomes) and depression and quality of life (secondary outcomes).

The aim of our study is to develop a methodologically sound and effective protocol that may serve as the foundation for a subsequent randomized clinical trial (RCT) to test the efficacy of EFT for the resolution of emotional injuries related to interpersonal offenses, in individuals aged 65 and older. In essence, a feasibility study such as the one proposed here, functions as a tool to assess the viability of the main trial (RCT)—specifically in terms of recruitment, retention, measurements, and other parameters—without necessarily focusing on clinical outcomes [22,27–29].

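### Control-group Pearson correlations cannot show average change over time, and no stated estimate uses the randomised comparison for the secondary objective

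*Protocol article*

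**What the plan says.** All references are to the protocol article.

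- **Secondary objective.** The aim is "To explore the outcomes of EFT for the resolution of emotional injury among the study’s participants", measured by forgiveness and letting go, and by depression and quality of life.
- **Participants.** At least 35 people per arm are randomised. Besides feasibility and acceptability, the aims include the therapy's effects: "as well as obtaining preliminary insights into its potential effectiveness among the participants involved".
- **Quantitative analysis, general approach.** For treatment outcomes, "the primary focus is not to test formal hypotheses but rather to provide an initial descriptive overview of the data". The authors continue: "we have chosen to employ descriptive statistics such as means, standard deviations, frequencies, and percentages to summarize the results".
- **Quantitative analysis, change over time.** One further outcome analysis is named. Its purpose comes first: "To identify and quantify potential associations among the different variables for the main trial". Then comes the method: "Pearson correlations will be performed to analyze observed changes over time in the control group for all outcome variables".
- **Study setting.** Intention-to-treat and completer analyses are both mentioned, without a contrast to which either applies. For the secondary objective, special attention goes to completers.

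No section names a difference between arms, an interval or a model for the clinical outcomes.

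**The concern.** The statistic, the group and the objective do not fit together. The sentence assigns a correlation to the analysis of change, but a correlation measures how closely two variables move together across people, not how far the group has moved. It then restricts the analysis to the arm still waiting for therapy, while the objective concerns outcomes of the therapy.

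The waiting list exists to separate the effect of EFT from what happens anyway over twelve weeks: natural improvement, regression to the mean and repeated questionnaires. If outcomes are summarised without an arm contrast and with emphasis on completers, improvement from these sources, or from selective dropout, can pass for a result of therapy. The abstract lists promising results among the conditions for a large trial, so the reading of these outcomes has some weight even though no hypothesis is tested.

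**Working it through.** The plan gives no effect size, SD, alpha or power for the clinical outcomes, so there is no figure of its own to reproduce. Three checks apply.

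**1. Can the statistic show average change?**

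For baseline X and later score Y, r = cov(X, Y) / (SD(X) × SD(Y)). Adding a constant c to every Y moves the mean of Y by c and leaves all deviations from the mean as they were. Hence corr(X, Y + c) = corr(X, Y).

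Numerical confirmation used 35 simulated pairs (X standard normal, Y = 0.6X + 0.8 × independent noise):

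| Shift added to every final score (SD) | Pearson r | Mean change (SD) |
|---|---|---|
| 0 | 0.5885 | −0.17 |
| +0.5 | 0.5885 | +0.33 |
| +2 | 0.5885 | +1.83 |
| −2 | 0.5885 | −2.17 |

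The sentence could instead mean correlating the change scores of different outcomes with one another. The same property holds: in a second simulated set of 35, r was 0.5197 with or without a mean change of 1 SD added to both variables. On either reading, r reflects rank stability or joint variation, not average change.

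**2. Does the group match the objective?**

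The objective concerns outcomes of EFT. Until the wait ends, the control arm has had none. A within-arm statistic for that arm carries no information on EFT against waiting. The intervention arm is not mentioned in the sentence.

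**3. What could the randomised comparison give?**

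Inputs: n = 35 per arm (Participants section), and a baseline to week-12 correlation ρ of 0.5, 0.6 or 0.7. The values of ρ are assumptions; the article gives none.

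Unadjusted 95% half-width in SD units = t(0.975, 68) × √(2/35) = 1.9955 × 0.2390 = 0.477.

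Adjusted for baseline, multiply by √(1 − ρ²), ignoring the one degree of freedom lost:

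| ρ (assumed) | √(1 − ρ²) | Half-width (SD) |
|---|---|---|
| 0.5 | 0.866 | 0.413 |
| 0.6 | 0.800 | 0.382 |
| 0.7 | 0.714 | 0.341 |

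Adjustment thus narrows the interval by about 13% (1 − 0.866) to 29% (1 − 0.714), using baseline scores that are already collected. For comparison, a correlation of 0.5 observed in 35 controls has a Fisher 95% interval of about 0.20 to 0.71.

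**The case against.** The strongest reply is that the sentence states its purpose, associations for planning the main trial, and that Pearson r is a proper tool for it. A baseline to follow-up correlation in untreated controls is a useful planning quantity, so restricting it to that arm is not in itself a fault. This stands, and the fix keeps it. It does not rescue the main clause, which gives the correlation the task of analysing change.

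A second reply is that the study is a feasibility trial that openly declines hypothesis tests and causal claims, and that a condensed article leaves table layout and intervals to fuller documents. Declining tests is legitimate and is not criticised here. But the section says which analyses were chosen, and its only sentence on change names an unsuitable statistic in one arm. That is a stated choice, not a detail left out.

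Two stronger readings are tempting, and the article supports neither:

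- A reader might infer that improvement in the control group would go unseen. Means and SDs are planned, the list of descriptive statistics is not closed, and nothing confines them to one arm. If tabulated by arm and visit, they would show such a change. The text simply does not say that they will be.
- A reader might infer that the main trial depends on the missing arm difference. The progression criteria use credibility and expectancy, session satisfaction, recruitment, retention, questionnaire response and homework, and no clinical outcome. The quantitative analysis section also says that the future sample size will rest on clinically meaningful effects rather than on provisional estimates from this study.

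**Conclusion.** The point holds at moderate weight, for the exploratory secondary objective only. Pearson correlations in the control arm can serve planning. They cannot show average change, and they say nothing about EFT. Beyond descriptive statistics of unspecified layout, no stated estimate uses the randomised comparison, and the emphasis on completers moves the description further from it.

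The estimate forgone would be imprecise: about ±0.48 SD unadjusted, and about ±0.41 to ±0.34 SD adjusted, given 35 analysed per arm and an assumed baseline to week-12 correlation of 0.5 to 0.7. It could not establish efficacy, but it is the one summary that separates therapy from waiting. The invariance of r needs no assumption. The primary objectives, the progression criteria and the basis of the future sample size are unaffected.

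**What to change.** Replace the sentence on Pearson correlations with text to this effect:

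*For each outcome we report the mean (SD) by arm and visit, and the mean change from baseline with a 95% confidence interval in each arm. We also report the between-arm difference at week 12, the end of the waiting period, adjusted for the baseline score, with a 95% confidence interval, in participants as randomised and without a hypothesis test. Pearson correlations, such as baseline to week 12, are reported only as planning values for the main trial.*

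Week 12 is the right point for the contrast because the control arm starts therapy afterwards. A completer summary can stand beside the as-randomised one, labelled as supplementary.

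The cost is one paragraph of text and a simple linear model per outcome in the software already named, with no new data or visits. The intervals will be wide, and the report must say that they are not evidence of efficacy. Recruitment had not started when the article was written, so the change can be made beforehand.
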